# Effect of electrical impedance-guided PEEP in reducing pulmonary complications after craniotomy: study protocol for a randomized controlled trial

**DOI:** 10.1186/s13063-022-06751-6

**Published:** 2022-10-01

**Keywords:** Randomized controlled trial, Individualized PEEP, Pulmonary complications, Craniotomy

## Abstract

**Objective:**

The purpose of this study is to explore whether electrical impedance tomography (EIT)-guided individualized positive end-expiratory pressure (PEEP) can reduce the incidence of pulmonary complications within 1 week following a craniotomy compared with a single PEEP (PEEP = 6 cmH_2_O) from dura suturing to extubation.

**Methods:**

A randomized controlled trial will be conducted at the Second Affiliated Hospital of Soochou University. Five hundred forty patients undergoing a craniotomy in the supine position will be randomly allocated into the P6 (PEEP = 6 cmH_2_O) or Pi (individualized PEEP) group. Both groups of patients will receive a lung recruitment maneuver before suturing the dura. Then, the P6 group will receive 6 cmH_2_O PEEP, and the Pi group will receive EIT-guided individualized PEEP. The incidence and severity score of pulmonary complications within 1 week following surgery, the lung ultrasound score (LUS), regional cerebral oxygen saturation (rScO_2_), and PaO_2_/FiO_2_ before anesthesia (T0), 10 min after extubation (T1), 24 h after extubation (T2), and 72 h after extubation (T3) will be compared between the two groups. The duration of surgery and anesthesia, the level and duration of PEEP during surgery, the volume of liquid intake and output during surgery, and the postoperative ICU and hospital stays will be recorded. The main outcome of this study will be the incidence of pulmonary complications within 1 week after surgery.

**Discussion:**

The purposes of this study are to determine whether EIT-guided individualized PEEP from the beginning of dura suturing to extubation reduces the incidence of pulmonary complications within 1 week after a craniotomy compared with a single constant PEEP and to evaluate the length of ICU and hospital stays. If our results are positive, this study will show that EIT-guided individualized PEEP is better than a single constant PEEP and can further improve the prognosis of neurosurgical patients and reduce hospitalization costs, which will promote the wide application of individualized PEEP in clinical anesthesia.

**Trial registration:**

Chinese Clinical Trial Registry CHiCTR2100051200. Registered on 15 September 2021.

**Supplementary Information:**

The online version contains supplementary material available at 10.1186/s13063-022-06751-6.

## Introduction

Postoperative pulmonary complications (PPCs) are common, with an incidence of 39% [1–3]. Miskovic et al. [4] broadly described PPCs as “complications affecting the respiratory system after anesthesia and surgery,” while most studies describe PPCs as atelectasis, pneumonia, pulmonary edema, exacerbation of underlying chronic lung disease, or postoperative respiratory failure [5]. Patients undergoing a craniotomy are exposed to intraoperative mechanical ventilation, postoperative bed rest, limb paralysis, and other factors for a long time, thus resulting in obstruction of sputum drainage, which significantly increases the risk for PPCs [6, 7]. In addition, a postoperative state of low consciousness caused by postoperative hydrocephalus, posterior fossa edema, surgical site hematoma, brainstem infarction, and meningitis are independent predictors of PPCs in neurosurgical patients [8, 9]. PPCs have adverse impacts on prognosis, including an increased ICU occupancy rate, prolonged hospital stay, perioperative mortality, and increased hospitalization costs for non-cardiothoracic surgery patients [10–12].

Protective lung ventilation (PLV) strategies have been adopted by many anesthesiologists and are widely used in clinical anesthesia [13, 14]. A low tidal volume combined with positive end-expiratory pressure (PEEP) ventilation and an alveolar recruitment maneuver (ARM) are the most widely used PLV strategies and can reduce lung volume and pressure injuries, improve lung function, and reduce PPCs [15]. Intraoperative mechanical ventilation combined with PEEP has value in the prevention and treatment of postoperative atelectasis and other pulmonary complications, but the level of PEEP required among patients varies greatly. A single PEEP does not consider the individual differences between patients, which may affect the effect of PLV. If PEEP is too low, atelectasis cannot be prevented. If PEEP is too high, a lung pressure injury might occur and the thoracic pressure will be increased which together will be unfavorable with respect to blood reflux, thus affecting circulation stability [16, 17]. For patients undergoing craniotomy, PEEP may also affect intracranial pressure (ICP) and brain-blood reflux, affecting the surgical process and patient recovery.

Electrical impedance tomography (EIT) measures the changes in electrical impedance under different ventilation conditions and dynamically monitors the ventilation distribution in different lung regions in real time [18]. EIT has the outstanding characteristics of non-invasiveness, radiation-free, and portable, which makes EIT possible for patients with mechanical ventilation under general anesthesia to quickly obtain individualized PEEP.

At present, individualized PEEP is mainly used for the study of postoperative atelectasis and static compliance [19, 20]; the impact of individualized PEEP on the incidence and severity score of PPCs has not been reported. The use of PEEP during craniotomy may affect cerebral blood flow reflux, lead to brain tissue swelling, and affect the surgical procedure. After lesion clearance, it often takes some time from dura suturing to extubation. Individualized PEEP ventilation during this time can not only avoid the impact on surgery, but also may reduce the incidence of PPCs. The purpose of this study is to determine whether EIT-guided individualized PEEP during the time from dura suturing to extubation reduces the incidence of pulmonary complications within 1 week after craniotomy. Other outcomes include the severity of pulmonary complications within 1 week, the lung ultrasound score (LUS), regional brain oxygen saturation (rScO_2_) and PaO_2_/FiO_2_ (before anesthesia and 10 min, 24 h, and 72 h after extubation), and the postoperative ICU and hospital stay.

## Methods

### Study design

This is a single-center, randomized controlled, single-blind trial that has been approved by the Ethics Committee of the Second Affiliated Hospital of Soochou University (no. JD-LK-2018-077-01) and registered in the Chinese Clinical Trial Registry (ChiCTR, no. CHiCTR2100051200). The framework of the study is to explore the superiority of individual PEEP compared with single PEEP. The schedule of enrollment, interventions, and assessments is shown in Fig. 1. The Standard Protocol Items: Recommendations for Interventional Trials (SPIRIT) checklist is provided as Additional file 1.

**Fig. 1 Fig1:**
[figure not shown]
Schedule of enrollment, interventions, and assessments

### Selection and withdrawal of patients

#### Recruitment

Patients admitted to the Neurosurgery Department of the Second Affiliated Hospital of Soochow University for supine surgery under general anesthesia will be screened and recruited during a routine preoperative evaluation. The basic patient information is shown in Table 1. Participants who meet the inclusion criteria will be required to sign an informed consent. The designated staff who performs the preoperative visit will be responsible for obtaining the informed consent.

**Table 1 Tab1:** Baseline patient characteristics

Variables	P6 group	Pi group	*P* value
Gender (male/female)			
Age (years)			
Height (cm)			
Weight (kg)			
BMI (kg/m^2^)			
ASA classification (I–II)			
Smoking (cases): never/ever/within 1 month before surgery			

#### Inclusion criteria

The inclusion criteria will be as follows: (1) patients undergoing elective craniotomy in the supine position, (2) 18–65 years of age, (3) American Society of Anesthesiologists (ASA) classification I–II, (4) 18.5 kg/m^2^ < BMI < 28 kg/m^2^, and (5) agree to participate in this study and sign an informed consent for anesthesia.

#### Exclusion criteria

Patients will be excluded from the study if they have any of the following conditions: (1) decline to participate in the study; (2) chronic lung diseases such as asthma, COPD, restrictive diseases, pneumonia, atelectasis, pleural effusion within 1 month before surgery, and acute lung injury caused by various reasons; (3) history of lung surgery, (4) abnormal cardiac function, (5) intracranial hypertension; and (6) preoperative CT or MRI showing midline deviation and ventricular compression.

#### Randomization

All participants who meet the inclusion criteria will be randomly divided into two groups, P6 group (PEEP = 6 cmH_2_O) or Pi group (individualized PEEP) in a ratio of 1:1. Randomization will be achieved using a computer-generated randomization table. The designated staff will perform the allocation sequence and assign participants to the interventions. This research staff will implement the distribution sequence through sealed and opaque envelopes. Participants will not open the corresponding envelopes until they have completed the experiment. The patients, surgeons, and staff involved in data collection and follow-up visits will be blinded to the grouping; however, the anesthesiologist responsible for the implementation of anesthesia will be aware of the grouping.

### Methods

#### Related parameter setting during operation

Upon receiving the patients in the operating room, the following will be monitored: noninvasive blood pressure, electrocardiogram (ECG), and pulse blood oxygen saturation. Invasive arterial pressure will be monitored by radial artery catheterization under local anesthesia. After completing the spontaneous breathing data record, intravenous anesthesia induction will be administered and endotracheal intubation will be performed: fentanyl, 5 μg/kg; etomidate, 0.3 mg/kg; and rocuronium, 0.6 mg/kg. After confirming the correct placement of the endotracheal tube, the Primus anesthesia machine (Drager, Germany) will be connected to the tube and volume-controlled mechanical ventilation will be initiated with the following parameters: tidal volume, 7 mL/kg; inhalation-expiration ratio (I: E) = 1:2; and oxygen flow, 1 L/min. The respiratory rate will be adjusted, and the partial pressure of exhaled carbon dioxide (PetCO_2_) will be maintained at 30~35 mmHg. Sevoflurane (1%) combined with propofol and remifentanil will be used to maintain anesthesia, and the bispectral index (BIS) will be maintained at 45–55. During the surgical procedure, fentanyl will be intermittently injected to deepen anesthesia, and rocuronium will be intermittently injected to maintain the single muscle twitch stimulation (T1/T0) on the muscle relaxation monitor < 25%. The intraoperative fluid intake and urine volume will be monitored closely. The tidal volume and drug dosage will be calculated according to the estimated body weight. The formulae to calculate the estimated body weight [21] are as follows: female (kg) = [height (cm) − 152.4] × 0.91 + 45.5 and male (kg) = [height (cm) − 152.4] × 0.91 + 50. All patients will receive an intravenous drip of 20% mannitol (1 g/kg) before opening the dura, and the head will be kept high and feet low (15°) during anesthesia and surgery. The indications for extubation will be an awake and cooperating patient and muscle relaxation monitoring train-of-four (TOF) stimulation > 90% [22]. The invasive blood pressure of patients before anesthesia induction will be designated as the basic blood pressure. When the systolic blood pressure, diastolic blood pressure, and mean arterial pressure (MAP) are 20% lower than the basic blood pressure or the MAP is < 60 mmHg, 0.1 mg/kg of ephedrine will be injected intravenously to increase the blood pressure. Any treatment that affects the stability of vital signs and is adverse to the rehabilitation of the patients is prohibited.

Based on the different options for lung protective ventilation during operation, the patients will be randomly allocated into two groups (P6 or Pi groups). In order to avoid the influence of PEEP on cerebral blood flow and intracranial pressure and thus affect the exposure of surgical field, PEEP (PEEP = 0 cmH_2_O) will not be used in both groups during the period from tracheal intubation to dura mater suturing. At the beginning of dura suturing, patients in both groups will undergo a lung recruitment maneuver. The airway pressure will be maintained at 30 cmH_2_O for 30 s [23], then the PEEP will be increased from 0 to 10 cmH_2_O in a 2-cmH_2_O gradient, and each gradient will be maintained for 1 min [24]. After the lung recruitment maneuver, 6 cmH_2_O PEEP will be used in the P6 group and EIT-guided individualized PEEP will be used in the Pi group until the endotracheal tube is removed. In the pre-test, the median of the best PEEP is 6 cmH_2_O, so we plan to compare individualized PEEP with a single PEEP ( PEEP = 6 cmH_2_O ). The EIT-guided individualized PEEP titration method is as follows [19]: all patients will wear an EIT (PV500, Dräger, Germany) electrode belt (including 16 electrodes) before anesthesia. During the increase in PEEP from 0 to 10 cmH_2_O, the data of pulmonary electrical impedance at each PEEP will be obtained. The EIT Data Analysis Tool (6.1) will be used to analyze the insufficient ventilation and excessive expansion areas at different PEEP and plot a graph (Fig. 2). EIT-guided individualized PEEP is considered as the nearest PEEP above the crossing of the curves representing overdistension and collapse.

**Fig. 2 Fig2:**
[figure not shown]
EIT-guided individualized PEEP titration

#### Primary and secondary outcomes

The primary outcome of this study is the incidence of pulmonary complications within 1 week following surgery. According to the method adopted by Costa-Leme et al. [25], the modified PPC scoring table will be used as the standard to evaluate the incidence of PPCs after surgery. When a patient has any of the symptoms or signs in Table 2 (e.g., cough, atelectasis, dyspnea, bronchospasm, hypoxemia, hypercapnia, pleural effusion, pneumonia, pneumothorax, mechanical ventilation, endotracheal intubation, respiratory failure) or the score ≥ 1, it indicates that the patient has postoperative pulmonary complications: incidence of pulmonary complications (%) = number of cases with pulmonary complications/total number of patients in this group.

**Table 2 Tab2:** Modified scoring standard of PPCs

Postoperative pulmonary complication score	
**Grade 1**	- Dry cough.
	- Micro-atelectasis: abnormal pulmonary symptoms or signs, body temperature excluding extrapulmonary causes > 37.5 °C; radiologic examination is normal.
	- Dyspnea, excluding extrapulmonary causes.
**Grade 2**	- Cough, expectoration, excluding extrapulmonary causes.
	-Bronchospasm: wheeze or the original wheeze requires changes in treatment.
	- Hypoxemia: SpO_2_ ≤ 90% when breathing air.
	- Atelectasis: radiologic evidence, with a body temperature > 37.5 °C or abnormal lung symptoms or signs.
	- Hypercapnia requiring treatment (PaCO_2_ > 50 mmHg).
**Grade 3**	- Pleural effusion requiring pleural puncture for drainage.
	- Pneumonia: radiologic evidence, accompanied by clinical symptoms (two of the following symptoms: leukocytosis or leukopenia, abnormal body temperature and purulent secretion, and pathologic evidence (Gram staining or bacterial culture) or the use of antibiotics need to be changed).
	- Pneumothorax.
	- Patients need non-invasive mechanical ventilation in all of the following situations: (a) blood oxygen saturation (SpO_2_) is < 92% during oxygen inhalation; (b) during oxygen inhalation, the oxygen flow needs to be > 5 L/min; and (c) respiratory rate ≥ 30 times/min.
	- Endotracheal intubation again after surgery, ventilator-dependent time (non-invasive or invasive mechanical ventilation) ≤ 48 h.
**Grade 4**	- Respiratory failure: the postoperative ventilator-dependent time exceeds 48 h or the ventilator-dependent time exceeds 48 h after re-intubation.
**Grade 5**	- Death caused by respiratory system failure.

^*^Only when two or more conditions occur at the same time, it is classified as grade 2

Bedside chest radiographs will be obtained for all patients at the first, third, fifth, and seventh postoperative days, in addition to those requested by the staff surgeons. They are independently analyzed by 2 pulmonary specialists, blinded to the grouping. Only concordant assessments (an abnormal opacity at the same location) will be integrated into clinical findings for the final score of pulmonary complications. The occurrence of pulmonary complications will be assessed daily, until the 7th day following surgery.

The secondary outcomes of this study are as follows:Severity of pulmonary complications within 1 week: The severity of pulmonary complications will be assessed daily, until 1 week after surgery, using the worst score within a week for analysis. The modified PPC scoring table will be scored on an ordinal scale ranging from 0 to 5, in which grade 0 represents no pulmonary complications, grades 1–4 represent gradually deteriorating pulmonary complications, and grade 5 represents death of patients caused by respiratory diseases before discharge (Table 2).LUS: Lung ultrasound examination will be performed using the 2−5-MHz convex array ultrasonic probe of Edge (Sonosite Corporation, USA) before anesthesia (T0), 10 min after extubation (T1), 24 h after extubation (T2), and 72 h after extubation (T3). Twelve lung regions will be examined [26]; the lung on each side is divided into two areas by the fourth intercostal space: the upper and lower lung areas, and the upper and lower lung areas of the right and left lungs are delineated by the parasternal, anterior axillary, posterior axillary, and paravertebral lines. Therefore, both lungs are divided into 12 areas according to body surface markers. According to the improved scoring table (Table 3), the highest LUS of each lung area is 3 points and the lowest LUS is 0 points. Therefore, the total score of LUS ranges from 0 to 36 points. The higher the LUS, the more severe the atelectasis in this area [27].Regional cerebral oxygen saturation (rScO_2_): The 5100C brain and regional blood oxygen detection system (Covidien Corporation, USA) will be used to monitor rScO_2_ at T0, T1, T2, and T3. The mean value of the bilateral rScO_2_ will be considered as the rScO_2_. To ensure the accuracy of data, rScO_2_ will be collected 3 times, with an interval of 10 s each time, and the average value of the 3 values will be calculated.Arterial oxygen partial pressure/inspired oxygen fraction (PaO_2_/FiO_2_): arterial blood will be collected at T0, T1, T2, and T3 for blood gas analysis to determine the PaO_2_/FiO_2_.Postoperative ICU and hospital stays.Other research indicators include the duration of surgery and anesthesia, level and duration of PEEP, blood loss volume, blood transfusion volume, fluid input and urine output during surgery, and dosage of anesthetics and ephedrine during surgery (Table 4).

**Table 3 Tab3:** Scoring criteria for lung ultrasound images

Score	Ultrasonic image
0 point	Clear A lines and pleural sliding sign with or without 0–2 B lines
1 point	≥ 3 B lines or small subpleural consolidations separated by smooth pleural lines
2 points	Multiple merged B lines or small subpleural consolidations separated by thickened and irregular pleural lines
3 points	> 1 × 2 cm subpleural consolidations

**Table 4 Tab4:** Intraoperative characteristics

Variables	P6 group	Pi group	***P*** value

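### The primary outcome is an incidence, but the cough items need not be new or worse than before surgery, so a pre-existing cough counts as a postoperative event in either arm.

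*Protocol article*

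**What the plan says.** The section Primary and secondary outcomes states: "The primary outcome of this study is the incidence of pulmonary complications within 1 week following surgery". The case rule follows: "When a patient has any of the symptoms or signs in Table 2", or a score of at least 1, the patient has a postoperative pulmonary complication. Assessment is daily to day 7.

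Four parts of Table 2 and the text around it bear on whether a finding must be new:

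- Productive cough, Grade 2: "Cough, expectoration, excluding extrapulmonary causes". Dry cough, Grade 1, carries no condition.
- Bronchospasm, Grade 2: "Bronchospasm: wheeze or the original wheeze requires changes in treatment". No other item refers to the patient's prior state.
- Atelectasis, Grade 2: "Atelectasis: radiologic evidence, with a body temperature > 37.5 °C or abnormal lung symptoms or signs".
- Films: "Bedside chest radiographs will be obtained for all patients at the first, third, fifth, and seventh postoperative days". Two blinded pulmonary specialists read them, and only findings on which they agree are used. The article states no comparison with a preoperative image.

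On who is eligible, Table 1 (Recruitment) lists "Smoking (cases): never/ever/within 1 month before surgery" as a baseline variable, so smokers are expected. The Exclusion criteria remove chronic lung diseases, recent pneumonia, atelectasis or effusion, and previous lung surgery. They do not mention smoking, cough or sputum.

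**The concern.** An incidence counts events that arise after the starting point. The case rule asks whether the patient has a sign, not whether it has appeared or worsened since surgery. A smoker who brought up sputum every morning before admission meets the productive-cough item on day 1. The qualifier about extrapulmonary causes does not help, because a smoker's cough is pulmonary.

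The PEEP strategy cannot prevent such an event. If the same share of patients in each arm enters the numerator this way, the reported incidence is too high, the risk difference shrinks and the relative risk moves towards 1. The worst-grade severity outcome uses the same table and inherits the same noise.

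The authors evidently saw the issue for one sign, because pre-existing wheeze counts only if its treatment must change. The Discussion also describes these complications as lung changes, which presupposes a baseline.

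**Working it through.** **Step 1: can a pre-existing finding meet the stated rule?**

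| Item | Condition besides the sign | Met by an unchanged pre-existing finding? |
|---|---|---|
| Dry cough (Grade 1) | none | Yes |
| Cough with expectoration (Grade 2) | extrapulmonary causes excluded | Yes, if the cause is pulmonary |
| Bronchospasm (Grade 2) | pre-existing wheeze needs a change in treatment | No |
| Atelectasis (Grade 2) | radiologic evidence plus temperature > 37.5 °C or abnormal lung symptoms or signs | Not by an opacity alone; possible with fever or a habitual cough |
| Pneumonia (Grade 3) | radiologic evidence plus further clinical criteria | Not by an opacity alone |

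The micro-atelectasis item excludes extrapulmonary causes of a raised temperature, but the atelectasis item does not. An old opacity that both readers accept, together with fever from any source, could therefore satisfy it.

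The footnote to Table 2 requires two or more conditions together for Grade 2. It governs the grade. It does not cancel the case rule, under which any listed sign suffices.

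**Step 2: reproduce the planned sample size.** Inputs from Sample size estimation and interim analysis: 24% (P6), 13.5% (Pi), α = 0.05, β = 0.2, dropout 20%. Sidedness is not stated; two-sided is used here.

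n = [1.960·√(2·p̄(1−p̄)) + 0.842·√(p1(1−p1) + p2(1−p2))]² / (p1−p2)², with p̄ = (0.24 + 0.135)/2 = 0.1875

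= [1.960·√0.3047 + 0.842·√0.2992]² / 0.105² ≈ 216 per group.

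216/(1 − 0.20) = 270. Both figures match the plan, with power 80.0%.

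**Step 3: reading (a), 24% and 13.5% are rates of new events and carried-over cases come on top.** Let f be the share of patients in each arm who are cases only because of a pre-existing finding. The document does not give f; 2% to 10% is assumed. The observed rate is p′ = f + (1−f)p, so the difference shrinks by the factor (1−f).

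For f = 5%: 0.05 + 0.95 × 0.24 = 0.278 and 0.05 + 0.95 × 0.135 = 0.178.

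| f | P6 | Pi | Difference (points) | Relative risk | Power at 216 per group | n per group for 80% |
|---|---|---|---|---|---|---|
| 0 | 24.0% | 13.5% | 10.5 | 0.56 | 80% | 216 |
| 2% | 25.5% | 15.2% | 10.3 | 0.60 | 76% | 240 |
| 5% | 27.8% | 17.8% | 10.0 | 0.64 | 70% | 277 |
| 10% | 31.6% | 22.2% | 9.5 | 0.70 | 60% | 345 |

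**Step 4: reading (b), the pre-test used the same rule, so its rates already contain such cases.** The planned 216 then still gives 80% under the present rule. The rate of new events is p = (p′ − f)/(1 − f). For f = 5%: (0.24 − 0.05)/0.95 = 0.200 and (0.135 − 0.05)/0.95 = 0.0895.

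| f | P6, new only | Pi, new only | Relative risk | Power at 216 per group | n per group for 80% |
|---|---|---|---|---|---|
| 2% | 22.4% | 11.7% | 0.52 | 84% | 193 |
| 5% | 20.0% | 8.9% | 0.45 | 91% | 158 |
| 10% | 15.6% | 3.9% | 0.25 | 98% | 101 |

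Both tables take f to be equal in the two arms and independent of the risk of a new event.

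**The case against.** **The article is a condensed text.** The schedule of assessments is a figure that is not shown, the full protocol is available on request, and the scale is adapted from a cited source. A reader might infer that symptoms are never recorded before surgery or that readers never see an earlier film. The article does not establish either. What stands is narrower: the article prints the case rule and the item definitions, and as printed they count an unchanged cough.

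**The document's own concept implies change.** The Discussion speaks of lung changes that affect prognosis, and the Introduction of complications after anesthesia and surgery. This shows the intent, but assessors score from Table 2, which does not carry it.

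**The exclusions narrow the problem.** The list of chronic lung diseases is open-ended and could take in chronic productive cough. Patients are 18 to 65 years old and ASA I–II, so most of the graver items are unlikely to be present before surgery. This stands. What remains is chiefly habitual cough.

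**Old opacities.** A reader might infer that an old scar agreed by both readers is an event in itself. It is not. Agreement is a filter, and every radiographic item also needs clinical criteria.

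**Power.** A reader might infer that the trial has only 60% to 76% power. That needs reading (a). The sample size section gives the pre-test rates for an outcome of the same name, so reading (b) is at least as natural, and under it the planned power is intact.

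**Bias.** Randomization, with blinded patients, data collectors and film readers, should make the error alike in both arms. That prevents a tilt towards one arm, but not dilution.

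**Conclusion.** The point holds for the two cough items and, in a limited way, for opacities that combine with fever or a habitual cough to complete the atelectasis item. Under the rule as printed, a pre-existing cough is a primary event regardless of the PEEP strategy. The result is non-differential misclassification: incidence is overstated and the relative risk is pulled towards 1. Nothing here suggests that one arm is favored or that the type I error rate is raised.

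The size is unknown. At an assumed 5% carry-over, reading (a) gives a relative risk of 0.64 instead of 0.56 and power of about 70% at 216 per group. Reading (b) leaves the planned 80% untouched, and a new-or-worse rule would raise power to about 91% at the same size. A loss of power against plan is therefore not established. On either reading the present definition measures something broader than a postoperative incidence. The correction is worth making because it is small and aligns the endpoint with the protocol's own description of it.

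**What to change.** Record the Table 2 symptom items for every patient at the preoperative visit or at T0, when lung ultrasound and blood gases are already taken. Define a primary event as an item that is new, or a grade worse, compared with that baseline. Score severity as the worst new or worsened grade. This extends the existing wheeze logic to cough.

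For films, instruct the two blinded readers to disregard an opacity already visible on an available preoperative chest image, in the same way in both arms. No extra imaging is needed. Patients without such an image stay under the present reading rule, and randomization should spread them evenly over the arms.

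The cost is a short checklist, a sentence in Table 2 and possibly a slightly lower event rate. Recruitment is under way, so the change should be settled before any comparison by arm, including the interim analysis. For patients already enrolled, baseline symptoms would have to come from existing records where these hold them. An analysis under the present rule can be kept as a sensitivity analysis.
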